## 3. Methods

### 3.1. Study Design

This study is a double-blind, parallel, 1:1 randomized controlled trial (RCT). After enrollment assessments, participants will be randomly assigned to either the experimental group, receiving the interactive podcast program, “Living with Type 1 Diabetes to Grown-Up,” or the active control group, receiving a sham treatment using an ineffective e-book, “Transitioning from Adolescence to Early Adulthood: The Ins and Outs of Type 1 Diabetes” which will be given at enrollment [57]. Both interventions will last for 3 months. Outcome measures will be evaluated at four time points: pre-randomization (T0), immediately postintervention (T1), 3 months post-intervention (T2), and 6 months postintervention (T3). This study has been registered at ClinicalTrials.gov (under identifier NCT06464640).  Figure 2 shows the detailed study process.

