### 3.3. Participants

#### 3.3.1. Eligibility Criteria

Participants will be recruited using convenience sampling. Inclusion criteria are as follows: (1) diagnosed with T1D by an endocrinologist before the age of 16, with a disease duration of more than 6 months, allowing sufficient time for diagnosis stabilization and self-care training [58, 59]; (2) aged between 16 and 25, representing the transition period from late adolescence to early adulthood [58, 60]; (3) mean HbA1c level ≥ 7.5% in the year before inclusion to identify patients who have inadequate blood sugar control, making them suitable candidates for the podcast intervention; (4) the ability to communicate in Mandarin or Taiwanese; (5) possession of a smartphone, tablet, or computer with Internet access, enabling program transmission and voice interaction for data collection; and (6) willingness to participate in the study with signed informed consent. For minors, the legal guardian must also provide signed informed consent. Individuals with other metabolic diseases, chromosomal abnormalities, major illnesses, or significant auditory and cognitive impairments will be excluded from this study, as these conditions may affect their healthcare needs and influence their understanding and utilization of the intervention [61, 62]. Participants using continuous glucose monitoring (CGM) will also be excluded from the trial, as its adoption remains low in Taiwan due to high out-of-pocket costs despite partial reimbursement [63]. This ensures consistency in glycemic data sources.

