#### 3.3.2. Sample Size Calculation

Few studies have explored podcast-based interventions for chronic diseases or illnesses in adolescents. As podcasting is a technology-based intervention method, results from our prior study of Healthcare CEO App [57] were used for sample size calculation. Effect sizes were calculated using Cohen's *d*. For groups of 19 participants each, the mean HbA1c for the experimental vs control group at 3, 6, and 9 months postintervention was 7.93 ± 1.36 versus 8.69 ± 2.40, 8.30 ± 1.29 versus 8.82 ± 2.69, and 8.24 ± 1.58 versus 8.87 ± 2.72, respectively, yielding an effect size of 0.38, 0.26, and 0.32, respectively.

Using G-Power 3.1.9.4 software, the required sample sizes were calculated for each group across the three time points as 18, 38, and 26 participants, respectively. Assumptions included two groups with four repeated measures, *α* set at 0.05, power at 0.80, and a correlation coefficient of 0.5. No participants withdrew from our prior study [57]. However, considering a conservative dropout rate of 12% based on similar online intervention studies with a 6-month follow-up period [64], the number of participants was increased to 21, 44, and 30 per group. The maximum sample size calculated based on the smallest effect size at T2 was chosen. Therefore, the total sample size will be 88 participants.

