#### 3.7.2. Primary Outcome: Wellbeing—Disease Control Outcomes

Assessed through HbA1c, the percentage of self-monitored blood glucose readings within the 70–180 mg/dL range, the number of hypoglycemic events (blood glucose < 70 mg/dL), and the number of hyperglycemic events (blood glucose > 180 mg/dL) [70] will be noted. HbA1c will be recorded from electronic medical records after blood samples are collected during patient visits. The percentage of self-monitored blood glucose readings within the 70–180 mg/dL range will be calculated using the formula: (number of values within the 70–180 mg/dL range/total number of tests)∗100% [57].

A data downloader at outpatient clinics will be used to retrieve the past 3 months' blood glucose data and reset it to prevent data from overlapping or being overwritten. Subsequently, two data collection assistants will simultaneously review the data manually. If discrepancies arise, the principal investigator will verify the data. Finally, interrater reliability will be assessed using Cohen's Kappa coefficient to ensure consistency in their evaluations [71]. In cases of abnormal blood glucose values, such as hypoglycemia, if the participant follows up with a blood glucose check 15 min after consuming carbohydrates, only the first recorded value (i.e., the pretreatment blood glucose value) will be used for analysis. Commercial blood glucose meters can store 500–1000 data points, and participants typically measure 2–5 times daily. Therefore, based on prior studies, data coverage is not expected to be an issue [57].

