### 3.8. Statistical Analysis

Descriptive statistics such as frequency distribution, percentage, mean, standard deviation, and maximum/minimum scores will be utilized to characterize the subjects' demographics, disease characteristics, outcome variables at enrollment, and podcast usage. The efficacy of the intervention will be assessed using generalized estimating equation (GEE) modeling, which accommodates repeated measurements and deals with missing data effectively, following the intention-to-treat principle.

GEE will evaluate differences in outcome variables between experimental and control groups over time. Linear GEE models will be applied for all the continuous outcomes. The models will include fixed effects for the group (experimental vs. control), time (baseline, postintervention, and 3 and 6 months postintervention), and their interaction. The working correlation structure will be selected based on the quasi-likelihood under the independence model criterion [77]. Statistical significance will be determined at *p* < 0.05. All analyses will be conducted using IBM SPSS 26.0 for Windows.

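### The prior-year mean HbA1c is required at screening but serves only as an eligibility gate; using it with T0 HbA1c as a covariate would tighten the HbA1c comparison at almost no cost

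*Protocol article*

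**What the plan says.** Inclusion criterion (3) in section 3.3.1 asks for a "mean HbA1c level ≥ 7.5% in the year before inclusion to identify patients who have inadequate blood sugar control". The number of readings behind that mean is not given, nor whether the T0 reading can be one of them.

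Section 3.7.2 places HbA1c first among four disease-control measures that form the primary outcome, and says of its source: "HbA1c will be recorded from electronic medical records after blood samples are collected during patient visits".

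Section 3.8 lists the GEE terms: "The models will include fixed effects for the group (experimental vs. control), time (baseline, postintervention, and 3 and 6 months postintervention), and their interaction". Baseline is a level of time, so T0 HbA1c sits on the response side. No covariate is listed.

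Section 3.3.2 sizes the trial on HbA1c, with the smallest of three effect sizes (0.26) setting the number. It adds: "Assumptions included two groups with four repeated measures, *α* set at 0.05, power at 0.80, and a correlation coefficient of 0.5".

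**The concern.** When two HbA1c readings correlate 0.5, a single reading is a noisy guide to a participant's usual level. Earlier readings then hold information on later HbA1c that T0 alone does not. Screening has to obtain a summary of those readings for everyone, yet the analysis as written uses it only as a yes/no threshold at 7.5%.

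What is at stake is precision, on the comparison that determined the sample size and at a small planning effect. A prognostic covariate already in hand narrows the confidence interval and absorbs chance imbalance in long-run control, with no further patients, visits or blood tests.

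**Working it through.** **The plan's own figure.** Take a between-groups repeated-measures F test with m = 4 measures, ρ = 0.5, α = 0.05, and 0.26 entered as Cohen's f. The noncentrality at N = 76 is f²·N·m/(1 + (m−1)ρ) = 0.0676 × 76 × 4/2.5 = 8.22, and the power is 0.808. That gives 38 per group; 38/(1 − 0.12) rounds up to 44, or 88 in total. The stated number is reproduced. Below, 0.26 is treated as a standardized mean difference, which is what section 3.3.2 calls it. That is why the powers fall well under 80%; how 0.26 was entered is a separate matter.

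**Inputs.** From section 3.3.2: d = 0.26, 38 evaluable per arm, ρ = 0.5. Assumed, because the protocol does not say: ρ = 0.5 also holds between prior-year readings and T0-T3; the prior-year mean rests on k = 1 to 4 readings separate from T0; HbA1c is normal with SD 1 before selection.

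**Residual variance v, before allowing for selection** (the variance of the group difference is 2v/38)

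- Single visit, planned group-by-time contrast (change from T0): 2(1 − ρ) = 1.00.
- Single visit, T0 as covariate: 1 − ρ² = 0.750.
- Single visit, T0 plus prior-year mean, with m = k + 1: 1 − mρ²/(1 + (m−1)ρ). For k = 1, 1 − 0.5/1.5 = 0.667; for k = 4, 1 − 1.25/3 = 0.583. That is 11-22% below 0.750.
- Mean of T1-T3: (1 + 2ρ)/3 = 0.667 unadjusted; 0.667 − 0.25 = 0.417 with T0; 0.667 − 0.333 = 0.333 (k = 1) or 0.667 − 0.417 = 0.250 (k = 4) with both. That is 20-40% below 0.417.

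**Selection at 7.5%.** Criterion (3) truncates this very variable, which narrows its spread and so its added value. I simulated the same correlation model, keeping only draws whose prior-year mean exceeds a cut placed at the population mean or half a single-reading SD below it (position assumed). Selection leaves the variance after adjusting for both covariates almost unchanged, but lowers the T0-only variance. Power is Φ(d/√(2v/38) − 1.96) plus the negligible lower tail.

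| Contrast | k | Cut | v, T0 only | v, both | Variance cut | Power |
|---|---|---|---|---|---|---|
| Three-visit mean | 1 | mean | 0.370 | 0.334 | 10% | 46% to 50% |
| Three-visit mean | 1 | −0.5 SD | 0.380 | 0.333 | 12% | 45% to 50% |
| Three-visit mean | 4 | mean | 0.331 | 0.250 | 24% | 50% to 62% |
| Three-visit mean | 4 | −0.5 SD | 0.358 | 0.250 | 30% | 47% to 62% |
| Single visit | 1 | mean | 0.703 | 0.667 | 5% | 27% to 28% |
| Single visit | 4 | −0.5 SD | 0.691 | 0.583 | 16% | 28% to 32% |

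**Where the gain vanishes.** Under a pure AR(1) correlation, T0 already carries everything the earlier readings could offer, and the cut is 0%. It is also 0% if T0 is the only reading in that year. If prior readings correlate 0.4 with follow-up, power on the average (before selection) rises from 42% to 45-48%; at 0.3 the rise is under 1 point.

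**Does adding the covariate to the model in section 3.8 help?** No. With complete simulated data, 38 per arm and an exchangeable working correlation, I fitted the planned four-time-point GEE as it stands, with the prior-year mean added, and with that mean plus T0 added. The group-by-time estimate and its standard error agreed to at least 12 decimals in all three. A quantity constant over time within a participant cannot alter a within-participant change. With T1-T3 as responses and covariates on the right-hand side, a 300-run simulation (one prior reading, no selection) gave variance factors of 0.74 with T0 and 0.65 with both, against 0.89 for the planned contrast (theory 0.75, 0.667 and 1.00; Monte Carlo error about 8%).

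**The case against.** The best defence is that nothing here is wrong. A randomized comparison without covariates is valid, the protocol does not contradict itself on this point, and further covariates could be named in an analysis plan that is not shown. A reader might infer from the omission that the HbA1c result would be biased, or that the screening value will be thrown away. The documents support neither. Randomization protects the comparison, the data collection form is not shown, and HbA1c remains in the medical record. What stands against this defence is that section 3.8 does state the model terms, they leave the value out, and a better specification is available.

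A reader might also take the 20-40% and 11-22% reductions as the expected gain. They ignore the eligibility cut and are too high for this trial.

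It is fair to say, too, that the gain is measured against a T0-adjusted model that the protocol does not have, that the three-visit average is not a contrast named in section 3.8, and that only one of the four primary measures benefits. All of this stands and limits the point; none of it removes the point. The objection that leaving T0 out of the prior-year mean could leave some participants with no covariate value is also sound, and the fix avoids that.

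**Conclusion.** The point holds as lost precision in a valid analysis; it is a cheap improvement, not an error. Under the stated assumptions the prior-year mean removes about 10-30% of the residual variance of the three-visit average beyond T0 adjustment (about 4-15 points of power), and about 5-16% at a single visit (about 1-4 points). These sizes depend on the number of prior readings, their correlation with follow-up and where the 7.5% cut falls, none of which the protocol gives; the gain may be nil.

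The larger step is moving T0 from response to covariate, which takes the single-visit variance from 1.00 to 0.75 before selection. The prior-year mean adds to that step and does nothing without it, or without an equivalent constraint at T0. Nor would it bring power near 80% at d = 0.26: the best case above is 62%.

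**What to change.** In section 3.8, for HbA1c only, take T1, T2 and T3 as the responses, with group, time and group-by-time. Include T0 HbA1c and the continuous prior-year mean HbA1c used for criterion (3) as covariates. An essentially equivalent form keeps T0 as a response, constrains the group means to be equal there, and lets the prior-year mean enter with time-specific coefficients. Simply adding a covariate to the present four-time-point model is not enough.

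Use the eligibility mean as computed at screening, even where it contains T0, so that no participant lacks a value. With T0 also in the model this loses little: under the equal-correlation model, a five-reading mean that includes T0 gives the same 0.583 as four separate readings. Record the number itself, not only that the criterion was met, and fix both covariates before unblinding.

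The cost is a short rewording, one data field that screening already produces, and one or two degrees of freedom. If prior-year values predict weakly, the gain will be negligible and little is lost.

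### The GEE gives pre-randomization baseline its own free group effect; adjusting for baseline instead would sharpen every treatment contrast at almost no cost

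*Protocol article*

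**What the plan says.** Section 3.8 sets out the model for the efficacy analysis: "The models will include fixed effects for the group (experimental vs. control), time (baseline, postintervention, and 3 and 6 months postintervention), and their interaction". It applies widely: "Linear GEE models will be applied for all the continuous outcomes". The correlation structure is left to a data-driven choice: "The working correlation structure will be selected based on the quasi-likelihood under the independence model criterion". The section names no baseline covariate and no constraint that the arms share a common mean at T0.

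Section 3.1 fixes when baseline is taken: "Outcome measures will be evaluated at four time points: pre-randomization (T0), immediately postintervention (T1", with T2 and T3 following at 3 and 6 months after the intervention. Allocation is 1:1.

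Section 3.3.2 supplies the correlation used for planning: "Assumptions included two groups with four repeated measures, *α* set at 0.05, power at 0.80, and a correlation coefficient of 0.5". Its effect sizes are 0.38, 0.26 and 0.32. The smallest leads to 38 per group before dropout and 44 after it.

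**The concern.** T0 precedes randomization, so the expected group difference there is zero and any observed difference is chance. The planned model nevertheless estimates that difference freely. The model is saturated in group and time, so the group coefficient is the baseline difference and each interaction coefficient is the follow-up difference minus the whole baseline difference. Subtracting all of a chance imbalance, rather than the share that the baseline-to-follow-up relationship supports, carries baseline noise into the treatment effect.

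What is at stake is precision. The trial is small, and T0 is already collected for each outcome. A more precise estimate is available from the same participants, and the published model leaves it unused.

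**Working it through.** **Inputs.** Model terms from section 3.8; T0 before randomization and 1:1 allocation from section 3.1; r = 0.5, d = 0.26, 38 per arm and 12% dropout from section 3.3.2. Two-sided alpha of 0.05 is assumed, since the article does not state the sidedness.

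**The plan's own figure.** 38/(1 − 0.12) = 43.2, rounded up to 44 per arm and 88 in total, as stated. The 38 is recovered when 0.26 is entered as Cohen's f in a between-groups repeated-measures F test with four measures and r = 0.5. Whether that entry is right is a separate question. Only r = 0.5 and the 38 completers are used below.

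**What the planned coefficient estimates.** In simulated complete data (44 per arm, r = 0.5, 700 replicates), the interaction coefficient matched the raw difference in mean change to about 4 × 10⁻¹⁶ under exchangeable working correlation and 6 × 10⁻¹⁶ under independence. With 12% dropout and an exchangeable structure the two were no longer identical but correlated 0.99.

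**Variance with equal SDs at T0 and follow-up**, for one visit, in units of 2σ²/n:

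- change from baseline: 2(1 − r)
- follow-up only: 1
- baseline-adjusted: 1 − r²
- adjusted/change: (1 − r²)/[2(1 − r)] = (1 + r)/2

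| r | Change | Follow-up only | Adjusted | Adjusted/change |
|---|---|---|---|---|
| 0.3 | 1.40 | 1.00 | 0.91 | 0.65 |
| 0.5 | 1.00 | 1.00 | 0.75 | 0.75 |
| 0.7 | 0.60 | 1.00 | 0.51 | 0.85 |

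At r = 0.5, 38/0.75 = 50.7, so 38 completers per arm analysed with adjustment are worth about 51 analysed as planned. The confidence interval narrows by 1 − √0.75, about 13%. The follow-up-only contrast has the same variance as the change score at this correlation, so using it instead recovers nothing.

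**Power at d = 0.26, 38 per arm, r = 0.5.** The standard error is √(2/38) = 0.229 SD for change and 0.229 × √0.75 = 0.199 SD adjusted. Two-sided t-test power is 0.201 against 0.253; the normal approximation gives 0.204 against 0.257.

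**Unequal SDs.** Let s0 and s1 be the SDs at T0 and follow-up.

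- change: s0² + s1² − 2r·s0·s1
- adjusted: s1²(1 − r²)
- change minus adjusted: (s0 − r·s1)²

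The last line is never negative, and is zero only when s0 = r·s1. The article gives no baseline SD, so two assumed cases show the range at r = 0.5:

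- s0 = 1.5, s1 = 2.1: 3.51 against 3.31, a saving of 6%.
- s0 = 2.1, s1 = 1.5: 3.51 against 1.69, a saving of 52%.

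**Simulated precision.** Removing the baseline group effect under an exchangeable working correlation, which is another way of using baseline, cut the empirical variance to 0.78 of the planned model's with complete data (theory 0.75) and to 0.80 with 12% dropout. There was no visible bias.

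**The case against.** The strongest reply is that nothing here is an error. A GEE with group, time and their interaction, with baseline among the responses, is a conventional layout and gives valid, unbiased estimates under randomization. That stands: a reader might infer bias from the free baseline effect, and the documents do not support that.

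A second reply is that section 3.8 does not say the interaction coefficient is the treatment effect, so a follow-up contrast could be chosen later. That is true, but the contrast available from this model leaves baseline unused and, at r = 0.5 with equal SDs, is no more precise.

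A third is that an unseen analysis plan may adjust. The article itself lists the model terms, so such a plan would depart from the published text, which would still need amending.

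A fourth concerns size, and it stands. The ratio (1 + r)/2 needs equal SDs at T0 and follow-up. A reader might infer a loss at every correlation below 1 and for every outcome; the unequal-SD formula shows that the loss can be small or, at one point, nil.

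**Conclusion.** The point holds as a nearly free improvement in precision, not as a flaw in validity. With equal SDs, baseline adjustment has 0.75 times the variance of the change contrast at the plan's r = 0.5, and 0.65 to 0.85 times for r from 0.3 to 0.7. With unequal SDs the saving may be smaller or larger, and it vanishes only when the baseline SD equals r times the follow-up SD.

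Two stronger readings should be resisted. One is that adjustment brings the trial close to adequate power. Power of about 61% rising to 73% appears only if the true difference is 0.52 SD. The article's stated smallest effect is 0.26 SD; its 0.52 is a difference in HbA1c points (8.82 − 8.30). At 0.26 SD power stays near 25%. The other is that the HbA1c entry criterion makes the loss worse. Selection is on the mean over the previous year, not on T0, and regression to the mean is expected equally in both randomized arms.

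**What to change.** In section 3.8, define T1, T2 and T3 as the responses for each continuous outcome, with fixed effects for group, time, group-by-time, the baseline value of that outcome and baseline-by-time. State that the treatment effect is the adjusted group difference at each visit. This gains precision whichever working correlation is selected.

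Keeping T0 as a response and constraining the arms to a common baseline mean is an alternative only with a non-independence working correlation. Section 3.8 lets the quasi-likelihood criterion choose, and if it chose independence the constrained model would reduce to the follow-up-only contrast.

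The cost is a change of wording and a few model degrees of freedom. No new data are needed. It should be made before any outcome data by arm are seen, so that the adjustment cannot look data-driven.

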### 3.9. Podcast Voice Feedback Data Analysis

Thematic categorization and calculation of theme occurrence frequencies will be conducted to support process evaluation, particularly in understanding participant engagement and informing intervention fidelity.

### 3.10. Ethical Considerations

The study was approved by the Chang Gung Medical Foundation Institutional Review Board (Submission Reference: 202300552B0C601) on April 14, 2024, under the Declaration of Helsinki guidelines.

### 3.11. Validity and Reliability/Rigor

To maximize the validity and reliability of the study, we enhanced the intervention fidelity following the NIH Behavior Change Consortium [68] (see Section 3.6). The trial will follow the CONSORT 2010 guidelines [78].

## 4. Discussion

### 4.1. Strengths

This study will evaluate the efficacy of the interactive podcast program “Living with Type 1 Diabetes to Grown-Up” using a double-blind, parallel 1:1 RCT. The program has several strengths. First, its development is theory-based [51] and tailored to the healthcare needs of T1D patients in transition [14, 17], employing a user-centered approach for evaluation and testing [53–55]. The content, number of episodes, frequency, duration, and language are all designed to meet patients' expectations during this transition [56]. Second, the program's immediate personalized interaction through voice feedback enhances information exchange by avoiding traditional text or photo communication. This voice messaging approach improves content review, applicability to daily life, and professional support, increasing patients' motivation and willingness to engage [79]. This feature sets the program apart from existing podcasts, audiobooks, or certain YouTube content. Finally, TF is a significant factor affecting the efficacy of RCTs [80]. Therefore, both the experimental and control groups will implement methods to standardize treatments received and optimize TF, enhancing the credibility of the study findings [80]. Furthermore, in addition to the rigorous RCT design, this study has developed strategies to enhance TF based on existing literature and increased the number of research assistants. Comprehensive classroom and clinical shadowing training will ensure effective TF monitoring (File S1). These strategies allow for a more comprehensive analysis of the intervention's efficacy and help reduce bias in the study results.

